### Adverse events reporting

Serious adverse events will be self-reported at the 6 months (T2) and 12 months (T3) visits to CHC. These events include hospitalization longer than 24 hours, emergency room visits, and other potentially relevant adverse cases of death, acute cerebro-cardiovascular accident, and kidney failure. Research staff members will review the reporting and patient’s healthcare record to determine the correlation to the intervention and trial participation.

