### Withdrawal

Withdrawal criteria include the following: (1) the participant intends to drop out of the study; (2) the participant is unwilling to follow the study protocol such as not visiting the clinic as scheduled or having the lab tests performed; (3) the participant is withdrawn due to critical medical reasons. For patients who withdraw from the study, we will obtain a consent form to retrieve data directly from their electronic healthcare records (EHRs) in the CHCs and compare their outcome indicators with those from the patients who complete the study.

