### Study management

A steering committee has been established to serve as the main governing body of this study. It is composed of cardiologists and clinical research scientists from Shanghai Chest Hospital and epidemiologists from Shanghai JiaoTong University, School of Medicine. The major responsibility of the steering committee is to evaluate, advise on, and approve the study protocol with modifications, communicate with the Ethics Committee, and supervise the practice of community hypertension care in accordance with China’s national hypertension management guideline.

The sponsor of the project is Shanghai Chest Hospital, which is indemnified for any harms as the result of trial participation. A project management team consisting of the principal investigator and the clinical trial operation director has been formed to manage the everyday operation of the study. The operation director is responsible for all decisions on the trial management and intervention delivery.

An independent, external monitor will carry out onsite monitoring, overseen by the study sponsor, once every month at each site following the risk-based monitoring plan established for the study. Safety reporting will follow the safety guidelines of the Project Monitoring Plan, and all adverse events will be recorded in the database.

An Independent Data Monitoring and Safety Committee, consisting of physicians and bioethicists from Shanghai Chest Hospital and statisticians from Shanghai JiaoTong University, School of Medicine, has been established for the trial. This committee is independent from the sponsor and has no competing interests. The committee will be in charge of auditing the trial once every quarter and will meet every 6 months to oversee all ethical and safety issues of the study. The Committee Charter is available from the operation director who manages and coordinates the trial.

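### The only SAE capture route the article names is self-report at months 6 and 12, although death is among the listed events; separately, the monitoring committee is called independent of the sponsor that supplies its physicians and bioethicists

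*Protocol article*

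**What the plan says.** **SAE capture.** Adverse events reporting gives the method in one sentence: "Serious adverse events will be self-reported at the 6 months (T2) and 12 months (T3) visits to CHC". The events covered are hospital stays of more than 24 hours, emergency room visits and "other potentially relevant adverse cases of death, acute cerebro-cardiovascular accident, and kidney failure". A review step follows: "Research staff members will review the reporting and patient’s healthcare record to determine the correlation to the intervention and trial participation".

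**Related provisions.** Study management adds: "Safety reporting will follow the safety guidelines of the Project Monitoring Plan, and all adverse events will be recorded in the database". It also provides for an external monitor at each site every month. Under Withdrawal, for patients who leave, "we will obtain a consent form to retrieve data directly from their electronic healthcare records (EHRs) in the CHCs"; the stated use is to compare their outcome indicators with those of completers. Failing to attend scheduled visits is itself one of the withdrawal criteria.

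**Committee.** Study management states "The sponsor of the project is Shanghai Chest Hospital". It describes the Independent Data Monitoring and Safety Committee as "consisting of physicians and bioethicists from Shanghai Chest Hospital and statisticians from Shanghai JiaoTong University", and then says: "This committee is independent from the sponsor and has no competing interests". The committee audits the trial quarterly and meets every 6 months.

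**The concern.** The named source of SAE information is the patient, in person, at two visits. The gravest listed events are those that stop a patient from attending or speaking. A patient who has died cannot report it, one disabled by a stroke may not, and one who has stopped attending is not asked. If the sites follow the article literally, the safety database is most likely to be incomplete where completeness matters most, and the statement that all adverse events will be recorded cannot be met by this route alone.

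The second matter is a claim about oversight. Readers and the ethics committee rely on the statement that the body reviewing safety is independent of the sponsor. If its physicians and bioethicists come from the sponsor hospital, that stated property does not hold.

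**Working it through.** **1. Does any stated route find events in patients who cannot report?** The provisions, side by side:

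| Provision (section) | Stated purpose | Finds SAEs in patients who die, are incapacitated or stop attending? |
|---|---|---|
| Self-report at T2 and T3 (Adverse events reporting) | Capture of SAEs | No |
| Staff review of reports and healthcare record (same section) | Relatedness to the intervention and to participation | Could, but not stated |
| Health-record retrieval after withdrawal, with consent (Withdrawal) | Comparison of outcome indicators | Could, but SAEs not named; a patient who dies or is incapacitated cannot consent at that point |
| Monthly external monitoring (Study management) | Onsite monitoring under a risk-based plan | Not stated |
| Project Monitoring Plan (Study management) | Governs safety reporting | Unknown; not shown |
| Primary care physician (PCP) follow-up every 2 weeks to 3 months by stage (Group 1: usual care; Groups 2 and 3 also receive usual care) | Care | Sites may learn of events; no instruction to record them as SAEs is stated |

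Self-report is the only provision whose stated purpose is to find SAEs.

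**2. How many patients could be without a 12-month report?** Inputs are from Sample size and power calculation.

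- Plan's own figures: 88 / (1 − 0.20) = 110 per group; 3 × 110 = 330. These reproduce. The 88 also reproduces from a difference of 7 mm Hg, SD 16.5 mm Hg, two-sided 5% and 80% power.
- Expected dropouts at the planned rate: 0.20 × 330 = 66.

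The 66 is a ceiling at the planned rate. Some of these patients will have reported at T2, and consented record retrieval may cover others. It counts patients without a T3 report, not events missed.

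**3. How late could a reported event reach the committee?** The visits are 6 months apart, so an event just after one visit may wait up to 6 months for the next. The quarterly audit then adds up to about 3 months, giving 6 + 3 = 9 months at worst if the audit reviews SAEs. If only the 6-monthly meeting does so, the figure is 6 + 6 = 12 months. Both assume that no site learns of the event and records it in between.

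**4. Committee independence.** Three statements in one section: the hospital is the sponsor; the committee's physicians and bioethicists come from that hospital; the committee is independent from the sponsor. The first two contradict the third. The statisticians come from the university's medical school, which is not named as sponsor, so their affiliation does not contradict the claim as worded.

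**The case against.** The strongest reply is that this is a condensed article. It refers safety reporting to a Project Monitoring Plan, says all adverse events go into the database, and provides monthly monitoring and record retrieval after withdrawal. It nowhere says that self-report is the sole route, and the word may be loose drafting. PCPs also see patients between study visits. Much of this stands: a complete absence of other capture cannot be concluded. What remains is that the article does fix a method, that the method does not suit the events it lists, and that none of the other provisions is said to find SAEs.

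Three stronger readings are tempting, and the documents do not support them.

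- *A reader might infer that the trial cannot record deaths or events in dropouts.* Record review and consented retrieval exist and might reveal them; the Project Monitoring Plan might require it.
- *A reader might infer a biased safety comparison between arms.* The Discussion does expect that control patients in particular may miss visits or discontinue, and Groups 2 and 3 have more contact. But no between-arm safety analysis is stated, the T2 and T3 visits are the same in all arms, and the direction and size of any difference are speculation.
- *A reader might infer that the whole committee lacks independence because its statisticians share an institution with steering-committee members.* The claim made is independence from the sponsor, and the university is not the sponsor.

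It is also fair to object that CHC records may be imperfect for this purpose. The centers are tier 1 clinics, and nothing says that their records hold admissions or deaths elsewhere. This limits the remedy but does not remove the reason for it.

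**Conclusion.** Both parts hold in limited form. First, the article names self-report at two visits as the SAE capture route, lists events that patients may be unable to report, and does not say that record review or retrieval is used to find events. Followed as written, it can miss SAEs in patients who die, are incapacitated or stop attending. The number missed cannot be estimated, because no event rates are given. This conclusion assumes that the unseen Project Monitoring Plan does not already provide another route; if it does, the defect is one of wording in the article.

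Second, Study management contradicts itself on the committee's independence from the sponsor. This needs no assumption beyond the text, and an unseen charter would not change where the members come from.

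Neither part touches the systolic blood pressure endpoint or its analysis. Both should be corrected, because they concern the completeness of safety data and the accuracy of a published statement on oversight.

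**What to change.** **Adverse events reporting.** State that SAEs are found by a scheduled review of the CHC electronic health record for every randomized patient, including withdrawn patients who have consented, at the same interval in all three arms and timed to feed the committee's quarterly audit. Keep self-report at T2 and T3, and site recording of any event on learning of it, as supplements. If the Project Monitoring Plan already contains such a route, name it here.

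*Cost:* protocol wording and some query work by existing research staff. No new visits are needed, since these records are already used for screening, for withdrawn patients and for judging relatedness. *Limits:* CHC records may not hold every outside admission or death, and coverage of withdrawn patients depends on their consent.

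**Study management.** Either appoint the committee's physicians and bioethicists from outside the sponsor hospital, or remove the claim that the committee is independent from the sponsor. *Cost:* reappointment without enlarging the committee, or the deletion of one claim.

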## Discussion

China is experiencing an epidemic of chronic diseases, among which hypertension and its complications top the list [1, 26–29]. The traditional model of physician-centered clinic visit has proven ineffective, as a very small number of available PCPs is facing an ever-growing number of patients, leading to limited time to be spent on each patient for collecting information and making exams and therapeutic decisions. New initiatives aiming to improve the efficiency of care delivery such as adopting EHRs, promoting community healthcare guidelines, and using mobile healthcare technologies have been put into action, yet in China few RCTs have been conducted to validate their effectiveness [30]. The other challenge the community healthcare service is confronting is that PCPs may not have sufficient experience to identify and manage hypertension-relevant CVD complications in time. To fulfill the task of improving population BP control to contain CVD risks, the healthcare regulators in Shanghai, China are testing a novel hypertension management model — PCTM — in which PCPs are closely partnering with cardiologists from university hospitals in data sharing and disease treatment by taking advantage of a set of telemedicine tools that allow home-based telemonitoring, app-based lifestyle coaching and text consultation, and auto risk analysis to assist proactive intervention [31]. The present randomized trial is thus designed to provide evidence for future integration into the existing healthcare systems.

Trials from other countries have examined the effects of BP or diabetic control in various primary care setups, and most of these studies found improved outcome measures after interventions. In general, three types of interventional models can be differentiated. The first is patient-centered care delivery. This approach has been trialed to strengthen disease awareness and medication adherence, and recent studies of such often involve adoption of tele-healthcare tools such as an app, text messaging, or telemonitoring devices [32–39]. The second is provider-centered care delivery. The focus of this model is on physician support, with the assistance of nurses, clinical pharmacists, medical educators, dietitians, or clinical decision support algorithms [40–45]. The third and latest approach is centered on the combination of both models [46–51]. Meta-analyses of hypertension care studies and the results from a four-arm diabetic care study all lead to the conclusion that provider-assisted self-management is more effective in healthcare outcomes [9, 11, 52–55]. In contrast to these trials that recruited medical assistants such as nurses as PCP support for intervention, the current PCTM study has the objective to instead add specialists from secondary or tertiary medical centers to intensify the care process. This model is particularly designed to fit into the currently revamping scheme of China’s community healthcare system to support the hypothesis that extending the role of specialists and making them more available to community healthcare services can enhance their effectiveness.

Besides testing the efficacy of the intervention, this study will have several other impacts if successful. First of all, this model can be replicated to apply to the management of other chronic conditions, as the care of diabetes, cardiac disease, and asthma/chronic obstructive pulmonary disease follows similar clinical pathways of telemonitoring, lifestyle, and medical interventions. Next, it provides the feasibility and acceptability evidence of employing mobile technologies to deliver healthcare services by capitalizing on the world’s largest population pool of smart phone users. The upward trend of elderly people using mobile apps for social networking in large cities in China has prepared them with the skills and proficiency to receive clinical care through the mobile platform. Policy makers in other geographic regions across the country could therefore develop and roll out similar telemedicine services. Last but not the least, surveys led by various health bureaus all indicate that patients in China have the perception of receiving better quality of care if specialists from tertiary medical centers are members of their healthcare team. Therefore, the model of integrating specialist service may enhance patient adherence to coaching and medication and may eventually translate to medical outcomes.

We also acknowledge limitations in this study. First, this is an open-label trial, as both patients and physicians are aware of the grouping information. Patient bias, especially for those in the control group, may occur when they are not compliant with follow-up clinic visits and even choose to discontinue the participation, while physician bias may occur when they provide interventions to the test group patients. We attempt to address this issue through intensive training of participating physicians and research nurses prior to the beginning of this study, and by setting up a project management team to continuously oversee the study progress to ensure that the protocol is being properly followed. Second, the recruited patients may reflect only a subpopulation who are frequent users of smart phones and mobile apps. Their demographic and healthcare profile may be distinctive from the rest of the hypertensive population, who are of different ages, at different geographic locations, and have less access to the Internet. Finally, the present study only involves four CHCs and one university hospital in Shanghai; thus, the findings and the PCTM model under study may not be generalized to other regions in China.

### Trial status

This trial is ongoing. The study began in September 2016, and follow-up is expected to be completed by March 2018 (Additional file 2).

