## Methods/design

### Study design

The coordinated PCTM study is a 12-month, pragmatic three-arm trial aiming to compare two telemedicine-based hypertension interventions with usual care. Group 1 participants receive usual care (UC) that complies with China’s Hypertension Prevention and Treatment Guideline 2010 (the national guideline) [21]. Group 2 patients additionally receive a BP telemedicine system including a BP telemonitor and a mobile app. Group 3 participants receive all of the above plus coordinated services jointly provided by their PCPs and a designated team of cardiologists who have access to the secure CareLinker website and review patient data with PCPs once every 3 months. PCP-directed proactive interventions such as phone consultations, requests for an immediate clinic visit, or referrals may also be given to Group 3 participants if their relevant PCP receives alerts produced by the CareLinker cloud engine as a result of detecting abnormal BP variability. A total of 330 enrolled patients will be randomized to each group in a 1:1:1 allocation ratio, and all outcome measures will be assessed at baseline (T1), 6 months (T2), and 12 months (T3) throughout the study duration (Fig. 1). We hypothesize that timely healthcare information exchange and closer collaboration between PCPs and cardiologists will improve community BP control. The Standard Protocol Items: Recommendations for Interventional Trials (SPIRIT) checklist is presented in Additional file 1 [22].

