### Participant recruitment

We estimate that each participating CHC has at least 8000 registered patients with hypertension who have been receiving the regular community hypertension care (i.e., usual care), resulting in more than 32,000 patients being available for this recruitment. Potential participants are identified either through direct PCP referrals or by screening CHCs’ EHRs following three eligibility criteria: (1) age 21 years or older, (2) had uncontrolled BP in the previous 3 months, i.e., ≥140/90 mm Hg; (3) received high school or higher level of education. Eligible participants are first screened over the phone for interest in participation, experience in smart phone and app use, and willingness to provide the consent form. Those who remain eligible are invited to their registered CHC to attend the screening sessions with at least two PCPs and one research electronic engineer who instructs participants on the use of the BP telemonitor and ensures that participants have the appropriate Android or Apple smart phone to download and use the CareLinker app. If the participant has uncontrolled BP, as defined in the above inclusion criterion 5, during the screening visit and signs the consent, the research nurse will continue the procedure by collecting baseline laboratory tests and study questionnaires. The eligible patients will be randomized to the control or to one of the two intervention groups. The recruitment process is expected to take 12 months to complete from September 2016 to September 2017.

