### Outcomes

#### Primary outcome measures

The primary endpoint of the trial is changes in mean SBP from baseline (T1) to 12 months (T3) measured using the BP telemonitor (Bliss BL928). The 12 months BP readings will be determined by taking the average of three BP measurements at the follow-up visit to the CHC. All BP data are collected and uploaded simultaneously to the trial database.

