### Sample size and power calculation

The sample size required for this RCT is 330 patients based on the following assumptions. The RCT is powered to detect a clinically meaningful difference in average change between baseline and 12 months SBP of 7 mm Hg and DBP of 5 mm Hg between Group 1and Group 3. We assume that the standard deviation for difference in SBP from baseline to 12 months is 16.5 mm Hg and the difference in DBP from baseline to 12 months is 11.5 mm Hg. Using a two-sample comparison of the mean change between Group 1 and Group 3, a sample size of 88 patients per group is required to have 80% power at the 95% confidence level. This number is further adjusted to 110 per group to account for an estimated dropout rate of 20% during the 12 months follow-up. To reduce this potential dropout, we will provide all participants an additional 2 years of free health consultation services from PCPs and cardiologists as an incentive after they complete the trial. All analyses will be performed according to the intention-to-treat (ITT) principle.

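### The stated end of follow-up (March 2018) is about six months earlier than the protocol's own recruitment window and 12-month primary endpoint imply

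*Protocol article*

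**What the plan says.** Three statements in the protocol article bear on the calendar.

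- Participant recruitment: "The recruitment process is expected to take 12 months to complete from September 2016 to September 2017".
- Study design: "all outcome measures will be assessed at baseline (T1), 6 months (T2), and 12 months (T3) throughout the study duration". Primary outcome measures defines the primary endpoint as the change in systolic blood pressure (SBP) from T1 to T3. The eligibility section excludes patients unwilling to complete the 12-month intervention, so the 12 months apply to everyone.
- Trial status: "The study began in September 2016, and follow-up is expected to be completed by March 2018".

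Trial status also points to Additional file 2, which is not available here. No section that is available gives a common closing date, a shorter follow-up for late entrants, or an early end of recruitment. Database lock is mentioned only as the deadline for completing the SAP, without a calendar date.

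**The concern.** A patient randomized in September 2017 is due at T3 in September 2018, six months after follow-up is said to be complete. At least one of the two dates is therefore wrong.

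At stake is whether the primary endpoint will be observed in all randomized patients. The sample size assumes 88 evaluable patients per group, after a 20% dropout allowance that covers patients leaving the study and not patients whose T3 visit falls after closure. If March 2018 did govern closure, the mixed model and multiple imputation would have to stand in for primary outcomes that were never collected, in numbers the plan does not provide for.

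**Working it through.** **Inputs.** Recruitment September 2016 to September 2017 (Participant recruitment). T3 at 12 months (Study design; Primary outcome measures). Follow-up complete by March 2018 (Trial status). 330 patients allocated 1:1:1, so 110 per group. Target difference 7 mm Hg in SBP, SD of change 16.5 mm Hg, 80% power, 20% dropout (Sample size and power calculation). Two-sided 5% level (Statistical hypothesis, methods, and analyses). The article gives no accrual curve.

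**1. The plan's sample size reproduces.** n per group = 2 × (1.960 + 0.842)² × (16.5/7)² = 2 × 7.85 × 5.56 ≈ 87.2, rounded up to 88. With dropout, 88/(1 − 0.20) = 110 per group, 330 in total. Normal-approximation power at 88 per group is 80.3%. The date problem does not touch this calculation.

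**2. The end date does not reproduce.**

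- Last enrolment September 2017 + 12 months = September 2018, which is 24 months after the start.
- Stated end: March 2018, which is 18 months after the start.
- Working back, March 2018 − 12 months = March 2017, so the stated end needs recruitment to close after about 6 months and not 12.

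**3. Share without T3 if both dates were kept.** This is the share enrolled after March 2017.

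- Uniform accrual: 6 of 12 months, so 50%, or 165 of 330.
- Uniform accrual, varying the day within each stated month: the low end is start 1 September 2016, last entry 1 September 2017, cut-off 31 March 2017, where 1 − 211/365 = 42% (139 patients). The high end is 30 September 2016, 30 September 2017 and 1 March 2017, where 1 − 152/365 = 58% (193 patients).
- Other shapes, with cumulative accrual t^k evaluated at half time: k = 0.5 (front-loaded) gives 1 − 0.5^0.5 = 29%; k = 2 (slow start) gives 1 − 0.5² = 75%.

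**4. Illustrative power.** This is a completers-only two-sample comparison of Group 3 with Group 1, ignoring the overall F test that the plan requires first. Under uniform accrual, 110 × 0.5 × 0.8 = 44 per group. Power ≈ Φ(7/(16.5 × √(2/44)) − 1.960) = Φ(1.990 − 1.960) = 51%; the t-based value is 50%. With k = 0.5 there are 62 per group and power is 66%; with k = 2 there are 22 per group and power is 29%.

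**The case against.** Both dates are forecasts, and the later one stands under Trial status and not in the methods. Nothing in the article says patients will be cut off. The design sections apply 12 months to everyone, and the statistical section commits to every effort towards a complete dataset. March 2018 would fit about six months of recruitment plus 12 of follow-up, and with more than 32,000 hypertensive patients in the four centers for 330 places, faster recruitment is conceivable, though not documented. In that case no one loses T3. All of this stands.

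The power figure is also not that of the planned analysis. The plan has a covariate-adjusted mixed model and multiple imputation, and a patient enrolled as late as September 2017 would reach the 6-month visit (T2) in March 2018, so some information could come from T2. Truncation by calendar date would mainly cost precision, since patients are randomized 1:1:1 within each center. This stands too, which is why the figure is given only as an illustration.

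Two stronger readings are tempting. A reader might infer that about half the patients will miss the primary endpoint. The article does not support this: it does not tie March 2018 to database lock or to the end of visits, and it gives no accrual curve. A reader might also notice that March 2018 is when the last recruit reaches T2, and infer that follow-up has been cut to 6 months. That is a coincidence of dates, and the text states 12 months throughout.

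What the objection does not remove is the contradiction itself. Additional file 2 may show a timeline, but no figure can make both printed dates true.

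**Conclusion.** The protocol article contradicts itself on its calendar. Its recruitment window and 12-month endpoint put the last primary-endpoint visit in September 2018, about six months after the stated completion of follow-up. This part is certain and needs no assumption.

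The consequence is conditional. It ranges from nothing, if recruitment closes by March 2017 or if March 2018 is simply a wrong date, to about half of the primary outcomes not collected, if both dates are kept and accrual is uniform. The article does not say which case applies. The sample size, endpoint definition and randomization are unaffected. Because the trial is described as ongoing, the point should be settled before March 2018 is used for closing visits or locking data.

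**What to change.** Reconcile Participant recruitment with Trial status. Either move the expected end of follow-up to September 2018 or later, or, if recruitment closes by about March 2017, correct the recruitment window.

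In either case add a rule that does not depend on a forecast: follow-up ends, and database lock and the primary analysis take place, only after the T3 visit window of the last randomized patient has closed.

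If one of the dates is merely an error, the cost is a text correction. If March 2018 was the operational plan, the cost is completion about six months later, with visits that the design already requires.
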